**5. Methods: Participants, interventions and outcomes**

**5.1** **Study setting and procedure**

This prospective, open-label, randomized, parallel-controlled clinical trial is conducted in the Epilepsy Center at the West China Hospital of Sichuan University. This study aims to evaluate the efficacy and safety of PFO closure for relieving epileptic seizures in patients with refractory epilepsy accompanied by PFO of second-grade or higher levels of RLS (PFOC-RE). The trial was registered on November 11, 2022, and the enrollment of all participants began on December 1, 2022. This trial is registered in the Chinese Clinical Trial Registry (ChiCTR2200065681).

After completing clinical screening and signing an informed consent form, all participants are randomized in a 1:1 ratio into the intervention or control group. Subjects assigned to the intervention group will undergo a PFO closure procedure and receive antiplatelet therapy for 24 weeks, while those in the control group will only receive antiplatelet therapy for 24 weeks, which is consistent with the medication regimen of the intervention group. All participants will be followed-up for 48 weeks. During the follow-up period, seizure characteristics including frequency, duration, severity, quality of life, and adverse safety events will be recorded to evaluate the efficacy and safety of the trial. The overall design flow chart is shown in Figure 3, and the detailed study period is presented in Table 1.

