7.Participants with existing severe systemic diseases, such as digestive, circulatory, respiratory, liver, urinary, musculoskeletal, immune, or genetic metabolic diseases, whom researchers judge might be a potential impact on the results of the trial.

8.Participants who received head surgery or neuromodulation.

9.Participants under consideration for seizure-related surgery or any surgery involving general anesthesia, or who were already under general anesthesia four weeks before the screening period.

10. Participants who receive vaccinations during the screening period or four weeks before.

11. Participants preparing for pregnancy or breastfeeding during the trial period or three months after the study.

12. Patients who are participating in other interventional clinical studies during the trial.

13.Participants who are planning to travel or live abroad during the study period and cannot be followed-up.

14.Participants deemed inappropriate by the researchers for other reasons (need for detailed recording).

**Table 1. Schedule of enrolment, intervention and assessment according to the Standard Protocol Items: Recommendations for Interventional Trials (SPIRIT) statement**

|  | **Study Period** | | | | | | | | |
| --- | --- | --- | --- | --- | --- | --- | --- | --- | --- |
|  | **Screening** | **Enrolment** | **Allocation** | **Intra-operation** | **Post-operation** | | | | **Close - out** |
| **Time Point*** | **-7 to -2** | **-1** | **-1** | **0** | **4** | **12** | **24** | **48** |  |
|  | | | | | | | | | |
| **Screening** | | | | | | | | | |
| **General information** | **X** |  |  |  |  |  |  |  |  |
| **Eligibility screening** | **X** |  |  |  |  |  |  |  |  |
| **Epilepsy diary** | **X** |  |  |  |  |  |  |  |  |
| **Enrolment** | | | | | | | | | |
| **Informed consent** |  | **X** |  |  |  |  |  |  |  |
| **Allocation** |  |  | **X** |  |  |  |  |  |  |
| **Interventions** | | | | | | | | | |
| **PFO closure** |  |  |  | **X** |  |  |  |  |  |
| **Clopidogrel 75mg** |  |  |  |  | **X** | **X** |  |  |  |
| **Aspirin 100mg** |  |  |  |  | **X** | **X** | **X** |  |  |
| **Assessment** | | | | | | | | | |
| **Seizure frequency** |  |  |  |  | **X** | **X** | **X** | **X** | **X** |
| **Seizure duration** |  |  |  |  | **X** | **X** | **X** | **X** | **X** |
| **Seizure severity** |  |  |  |  | **X** | **X** | **X** | **X** | **X** |
| **Life quality** |  |  |  |  |  | **X** |  | **X** | **X** |

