**10. Outcomes**

**10.1 Primary outcome**

The secondary efficacy outcomes include the percentage decrease in the average duration of seizures after surgery compared with before, improvement in the severity of epilepsy after surgery, frequency of epileptiform discharge by 24h video EEG, evaluation of postoperative quality of life, improvement in migraine in patients with migraine complications, headache impact test, incidence rate of adverse events, cardiac ultrasound index, and some laboratory indicators.

The primary efficacy outcome of our trial is the percentage reduction in the frequency of epileptic seizures during the first year after surgery compared to before surgery. The seizures must conform to the description of seizure characteristics in the International League Against Epilepsy (ILAE), and the preoperative seizure frequency is measured in months and calculated based on valid seizure diaries only. The postoperative seizure frequency is calculated in the same way but should ensure that patients have valid seizure diaries for over 95% of the entire follow-up period.

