**11. Sample size calculation**

Prior to this study, we recruited 28 subjects with refractory epilepsy to undergo PFO closure surgery and followed them up for one year after the operation. The primary efficacy outcome of this trial is the percentage decrease in the frequency of epileptic seizures during the first year after surgery compared to before surgery. In the 28 patients, the mean percentage decrease was 49.60%, with a standard deviation of 41.67%.

Combined with the control group parameter settings in drug research on refractory epilepsy treatment, we estimate that the surgical group's average therapeutic effect in this study is 50%, with a standard deviation of 0.42. The average percentage decrease in the control group, based on previous literature, is set at 20%, with a standard deviation of 0.20. Therefore, with a superiority margin of 0.1, a single-sided alpha of 0.025, and a test power of 0.80, the total sample size required is 88. To account for possible subject withdrawal and loss of follow-up, we increase the sample size required by 20%. Therefore, we plan to recruit approximately 110 subjects for this study.

12. **Statistical analysis**

1.Program of analysis set

The complete analysis plan consists of three sets: Full Analysis Set (FAS), Per-Protocol Analysis Set (PPS), and Safety Set (SS). Both FAS and SS will include all participants who are randomly assigned, but those with serious protocol violations, active withdrawal, serious adverse events, or extremely poor compliance will be excluded from PPS. For FAS, we intend to follow the modified intention-to-treat (mITT) analysis principles, which will exclude participants without a PFO diagnosis confirmed by intracardiac echocardiography during the surgical procedure.

2.Missing data

In the event that patients are lost to follow-up during the study, their corresponding data will be carried over and included in the analysis. The evaluation process will be performed by the project team's doctors, and the data will be reviewed by the data monitoring committee.

3.Statistical analysis methods

The demographic characteristics of PRE receiving PFO closure and those not receiving it will be compared to assess bias and ensure accurate representation of the participants. Primary and secondary outcomes will be described statistically using mean ± standard deviation, median, minimum, maximum, and other indicators. Categorical data will be described using frequencies and percentages.

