The primary outcome of the trial will be analyzed using a mixed model of fixed and random effects, and factors with significant differences between the baseline datasets will be incorporated into the model as control variables. Additional analyses will include t-tests, chi-square tests, rank-sum tests, logistic regression, and propensity score matching to examine the secondary outcome indicators. Covariance analysis and mixed-effects models that consider the effect of time will be used to examine temporal trends in the clinical characteristics of epilepsy. All analyses will be performed using R-project version 4.2.1. Statistical significance will be set at two-sided p<0.05.

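### The primary outcome is one percentage per participant at one centre, and the trial is sized on it, but the primary analysis is a mixed model that does not fit that outcome

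*Protocol*

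**What the plan says.** Four parts of the protocol bear on this point.

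- **Outcome (Section 10.1).** The primary outcome is "the percentage reduction in the frequency of epileptic seizures during the first year after surgery compared to before surgery". Valid diaries must cover more than 95% of follow-up, which Section 5.1 sets at 48 weeks. This gives one number per participant.
- **Setting (Section 5.1).** The "clinical trial is conducted in the Epilepsy Center at the West China Hospital of Sichuan University". No other cluster is defined. Some later sections mention study sites, but none defines a site effect.
- **Sample size (Section 11).** Arm means of 50% (SD 0.42) and 20% (SD 0.20) are compared "with a superiority margin of 0.1, a single-sided alpha of 0.025, and a test power of 0.80". The result is 88, raised to about 110 for losses.
- **Analysis (Section 12, item 3).** "The primary outcome of the trial will be analyzed using a mixed model of fixed and random effects". Time-based models appear in a separate sentence with a different purpose: "Covariance analysis and mixed-effects models that consider the effect of time will be used to examine temporal trends in the clinical characteristics of epilepsy".

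Table 1 also schedules seizure frequency at weeks 4, 12, 24 and 48 and at close-out. No section links those visits to the primary model.

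**The concern.** A random effect needs repeated values within some unit. The primary outcome as defined supplies none: there is one value per participant and one centre. The named model and the named outcome therefore do not belong together.

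To use a mixed model in a meaningful way, the analyst must first replace the single percentage with repeated values and then decide which term is the treatment test. An average over follow-up, the last period and a group-by-time term answer different questions. Only the first resembles the quantity that was sized. In an open-label trial the primary test should follow from the protocol without such a choice.

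**Working it through.** **1. Reproduce the sample size.** Inputs from Section 11: difference 0.50 − 0.20 = 0.30; margin 0.10; SDs 0.42 and 0.20; one-sided alpha 0.025; power 0.80.

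Normal approximation: n per arm = (0.42² + 0.20²)(1.960 + 0.842)² / (0.30 − 0.10)² = 42.46, so 43 per arm.

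Noncentral t: 44 per arm, 88 in total, with power 0.805 (pooled) or 0.802 (Welch). For losses: 88 / (1 − 0.20) = 110.

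Both stated figures reproduce exactly as a two-sample t-test with one value per participant.

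**2. Put a mixed model on that outcome.** Write y = a + b·arm + u + e, one row per participant, with u the participant effect and e the residual. The variance of y is var(u) + var(e), and the likelihood depends only on this sum.

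One simulated data set (44 per arm, the protocol's means and SDs) confirms it. The log-likelihood is −18.14 whether 0%, 25%, 50%, 75% or 99% of the variance is assigned to u. The arm estimate is 0.2906 in the mixed fit and 0.2906 by least squares (least-squares SE 0.063). A random effect for the single centre fails in a similar way, because it cannot be separated from the intercept.

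**3. Use the visits instead.** A random-intercept model on four simulated visits per participant converged with identified variances, so the visits would support a mixed model. The question is what it would test.

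*Power.* The average SD is √((0.42² + 0.20²)/2) = 0.33, and it belongs to the whole-year value. Assume four equally weighted periods, a constant difference of 0.20 beyond the margin, equal SD s in each period and within-person correlation r. Then 0.33² = s²(1 + 3r)/4, so s = 0.33·√(4/(1 + 3r)). With 44 per arm the noncentrality is 0.20/(SD·√(2/44)).

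| Test | r | SD | Noncentrality | Power |
| --- | --- | --- | --- | --- |
| 48-week average | any | 0.33 | 2.84 | 0.80 |
| Last period | 0.4 | 0.445 | 2.11 | 0.55 |
| Last period | 0.6 | 0.394 | 2.38 | 0.65 |
| Last period | 0.8 | 0.358 | 2.62 | 0.74 |

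Weighting the periods by length (4, 8, 12 and 24 weeks) replaces (1 + 3r)/4 by 0.347 + 0.653r. Last-period power is then about 0.59, 0.68 and 0.75, so the conclusion is the same.

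*Size of effect.* Suppose, for illustration, arm differences of 0.10, 0.20, 0.30 and 0.40 at weeks 4, 12, 24 and 48. The week-48 effect is 0.40. The equal-visit average is (0.10 + 0.20 + 0.30 + 0.40)/4 = 0.25. The time-weighted average is (4·0.10 + 8·0.20 + 12·0.30 + 24·0.40)/48 = 0.317.

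**The case against.** **Repeated data exist, so a mixed model is possible.** This is correct. Table 1 schedules repeated assessments, and Section 10.1 measures frequency in months from diaries both before and after surgery. A reader might infer from the mismatch that no mixed model can be fitted in this trial. The documents do not support that, because the failure is confined to the single-percentage layout. What remains is that Section 12 assigns the model to the primary outcome as defined and gives time-based mixed models a different job. Nothing says that the primary model uses the visits.

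**The treatment effect survives even in the one-row layout.** This is also correct. A reader might infer that the effect cannot be estimated, or that its standard error would be too small by some fixed amount. Neither follows. The estimate equals least squares. The standard error that software reports from a forced fit varies with the optimiser and says nothing measurable about this plan.

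**The statistical analysis plan may settle it.** Random-effect structure and covariance detail may properly sit there, and their absence from the protocol is not the complaint. It also cannot be claimed that the test will be chosen after the data are seen. But the mismatch is between two protocol statements, so a later plan can remove it only by departing from Section 10.1 or Section 12.

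**A treatment-by-time slope would have almost no power.** A reader might add this, but it is not evidence here. Under a constant effect the slope is zero by construction, and the protocol does not make it a candidate for the primary test.

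**Conclusion.** The point holds as a mismatch between outcome, sample size and model. Sections 10.1 and 11 define and size one whole-year percentage per participant in one hospital, and Section 12 analyses it with a model that needs repeated or clustered values. On one row per participant only the variance split is unidentified. The sample size itself is sound for the comparison it describes.

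The practical consequence is that the protocol does not fix the tested effect if the visits are used. Power could be 0.80, or about 0.55 to 0.74, depending on whether the average or the last period is tested. That range assumes an SD of 0.33 for the 48-week value, a constant difference, equal period SDs and correlations of 0.4 to 0.8. The protocol gives no correlation. The plan should be changed, but nothing in the design or data collection is lost.

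**What to change.** Replace the primary-analysis sentence in Section 12, item 3, with one of the following.

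1. **Preferred, because it matches the sample-size basis.** A linear model of the single 48-week percentage reduction on arm, with baseline seizure frequency as a pre-specified covariate and heteroscedasticity-robust standard errors. The robust errors follow from the plan's own assumption of SDs of 0.42 and 0.20. Baseline frequency is already available from the screening diary.
2. **If a mixed model is kept.** Apply it to per-period seizure frequency with a participant random effect, define the periods, and name the arm contrast averaged over weeks 0 to 48 as the only primary test. State how that contrast relates to the percentage scale on which the 0.1 margin and the sample size are set.

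In either case keep the time-trend models secondary. The cost is one paragraph of wording. Option 1 needs no new data and no change to 88 or 110. Option 2 needs no new data, but a check that the sample size still holds on the chosen scale.

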**13. Oversight and monitoring**

A. Monitoring Procedures

As indicated by the guidelines established for Investigational Device Exemptions by the NMPA, the following monitoring procedures will be developed for this investigational study. Qualified monitors will be designated to assure that both the Sponsor and Investigators comply with protocol and regulatory requirements. Designee will communicate with each investigational site prior to the onset of the study to review relevant NMPA regulations, the Investigational Plan, IRB review and approval, completion and submission of forms, record keeping requirements, and administrative reports.

During the pre-investigational assessment, designee will assess the adequacy of the facilities, the availability of the Investigator, the potential number of study participants, and the provisions for staff support. To ensure that the Investigators and their staff understand and accept their defined responsibilities, designee will maintain regular correspondence and perform periodic site visits during the course of the study. This will verify the continued acceptability of the facilities, compliance with the Investigational Plan and relevant regulations and guidance documents, and the maintenance of complete records.

Routine monitoring visits will occur during the course of the study as defined in the Clinical Quality Plan. Monitoring will include review and resolution of missing or inconsistent results and source document checks (i.e. comparison of submitted study results to original source documentation) to ensure the accuracy of the reported data.

The monitor will evaluate and summarize the results of each site visit in written reports and a Summary of Visit letter to the Investigator. The Summary of Visit letter will provide documentation of what activities were conducted at the visit as well as any open action items/issues pertaining to the study following each monitoring visit.

Any repeated compliance issues and specific recommendations for resolution of noted deficiencies will be conducted in compliance with our Deviation Management system. The study Clinical Research Associate will promptly review all incoming data to identify inconsistent or missing data and adverse events. Data issues will be identified and addressed to the investigational site for resolution both before and during site visits. To ensure all data are confidential, designee will maintain secure hard copy forms and data files.

B. Data Management

It will be the responsibility of the Principal Investigator to complete and sign all case report forms. Data collected during this study will be analyzed. Additional cases may be performed during the review process and the results submitted to NMPA for review after the completion of the follow-up period previously outlined in this plan.

C. Records and Reports

Evaluation Report Forms

Investigators for this study will be thoroughly instructed in the components and use of the PFO Occluder. Subject case report forms will be distributed to each site before commencing the study. The Investigator, as well as the support staff, will be instructed in the details of the case report forms. A record will be created in a database for each patient in the study. Records will be updated as the study progresses. Additional case report forms will be supplied upon request.

Records are subject to NMPA inspection and must be retained by Investigators for a period of two years after the latter of the following dates:

The date on which the investigation is terminated or completed.

The date the records are no longer required for purposes of supporting an application to the NMPA to market the device.

Investigator Records

Investigators are responsible for maintaining the following records:

Correspondence with the NMPA, the Sponsor, IRB, and other Investigators relating to this investigation.

Record of receipt of the PFO Occluder, and necessary accountability records.

Patient records, including Informed Consent, copies of case report forms, and supporting documents (lab reports, etc.)

Study protocol with dates and reasons for deviations that may affect the scientific quality of the study.

Unanticipated adverse event reports.

Investigator Reports

Investigators are responsible for preparing and submitting the following reports. These reports are subject to NMPA inspection and the retention requirements previously described.

Unanticipated Adverse Effects Related to Device Use

Any occurrence of unanticipated adverse health effect of complications leading to serious injury or death which are associated with the PFO Occluder must be called in immediately (within 24 hours) and reported in writing to the appropriate IRB. This report must be submitted within ten (10) working days after the Investigator first learns of the effect.

Final Report

This report must be submitted within three (3) months after termination or completion of the investigation.

**14. Discussion**

Undeniably, the etiology of refractory epilepsy is complex and difficult to explore, and current drug therapy has not demonstrated satisfactory control efficacy. The PFOC-RE trail will be the first time in the world to preform PFO closure surgery on patients with refractory epilepsy, which may bring encouraging news. This study is hoped to achieve good treatment effects on patients with refractory epilepsy and PFO, including reducing the frequency of postoperative seizures and alleviating the symptoms of seizures.

Reviewing the previous research, the mechanism of PFO's impact on brain neurofunction has gradually been cleared, and there is ample clinical evidence of the health benefits of PFO closure in patients with cryptogenic stroke and migraines[12]. Our clinical trial may further expand the therapeutic value of PFO closure in brain neurofunction diseases. Importantly, our study results can not only provide clinical evidence for exploring the impact mechanism between PFO and refractory epilepsy but also may be used in future larger multicenter clinical trials to benefit more patients.

**15. Trail status**

The first patient was included in December 1, 2022. We expect to finalize the study in November 2026. Protocol version 1.0 document completed in December 2022.

**16. Abbreviations**

Patent Foramen Ovale Closure for Refractory Epilepsy: PFOC-RE; Patent foramen ovale: PFO; Right to left shunt: RLS; Randomized controlled trial: RCT; Electronic data capture: EDC; International League Against Epilepsy: ILAE; Minimum Mental State Examination: MMSE; Electroencephalo-graph: EEG; Full analysis set: FAS; Per-protocol analysis set: PPS; Safety set: SS; Modified intention-to-treat: mITT.

**17. Declarations**

**Ethics approval and consent to participate**

Ethical approval for this study has received from the Ethics Committee of West China Hospital of Sichuan University (No, HXDZ21006), and recruitment started in December 1, 2022. All participants are required to provide written informed consent. Our team confirm that all methods were performed in accordance with the relevant guidelines and regulations. Any protocol amendments will be approved by the appropriate research ethics committee. Study outcomes will be disseminated through peer-reviewed publications and academic conferences.

**18. Appendix**
